## Centre(s)

Seventeen hospitals in the UK.

## Design

The design is a double-masked randomised placebo-controlled trial, with embedded substudies to explore mechanism of action of metformin, in a population of ∼400 obese pregnant women (figure 1).

**Figure 1 BMJOPEN2014006854F1:**
[figure not shown]
Flow chart of participants in the trial.

## Inclusion and exclusion criteria

### Screening phase inclusion criteria

Caucasian obese (BMI ≥30 kg/m^2^) pregnant women between 12^+0^ and 16^+0^ weeks’ gestation;Age greater than or equal to 16 years;Signed informed consent form.

### Screening phase exclusion criteria

Non-Caucasian;BMI <30 kg/m^2^;Gestation >16^+0^ weeks;Pre-existing diabetes;Gestational diabetes in a previous pregnancy;Systemic disease at the time of trial entry, with the disease either requiring regular medication or having required treatment with systemic steroids in the past 3 months;Previous delivery of a baby <3rd centile by weight;Previous pregnancy complicated by pre-eclampsia prompting delivery before 32 weeks’ gestation;Known sensitivity to metformin hydrochloride or any of the excipients;Acute conditions at the time of trial entry with the potential to alter renal function such as dehydration sufficient to require intravenous infusion, severe infection, shock, intravascular administration of iodinated contrast agents;Acute or chronic diseases which may cause tissue hypoxia such as cardiac or respiratory failure, recent myocardial infarction, hepatic insufficiency, acute alcohol intoxication, alcoholism;Lactation;Multiple pregnancy.

### Randomisation exclusion criteria following screening

Gestational diabetes mellitus (GDM) in index pregnancy (diagnosed with 75 g oral glucose tolerance test using WHO criteria, see table 1). Participants are also excluded if glucose tolerance test is diagnostic of GDM based on the criteria used in the recruiting centre.Known liver or renal failure or dysfunction at the time of trial entry tested prior to randomisation (defined as variable above the reference range shown in table 2).

**Table 1 BMJOPEN2014006854TB1:** WHO diagnostic criteria for gestational diabetes following 75 g oral glucose tolerance test

Time (hours)	Blood glucose (mmol/L)
0	≥7.0
2	≥7.8

**Table 2 BMJOPEN2014006854TB2:** Reference ranges for biochemical parameters

Variable	Range
Urea	2.5–6.6 mmol/L
Creatinine	<85 μmol/L
Sodium	135–145 mmol/L
Potassium	3.6–5.0 mmol/L
Bilirubin	3–16 μmol/L
ALT	10–60 IU/L

ALT, alanine transaminase.

### Ineligible and non-recruited participants

No further information will be collected on women who are ineligible solely because of abnormalities in glucose tolerance, liver or renal function, other than the number of such women for inclusion in trial metrics.

Telephone or face-to-face interviews will be carried out to explore the reasons for eligible women declining to participate.

## Methods

We will recruit women attending maternity hospitals in the UK. Women who fulfil all the potential eligibility criteria and who express an interest in the study will be provided with the participant information sheet and given at least 24 h to consider participation. They will then be asked to provide written informed consent. Following consent, participants will have screening blood tests including liver and renal function and a 75 g oral glucose tolerance test, to determine eligibility for randomisation. Participants will have demographics, medical history, height, weight and anthropometry measurements (waist, hips, mid-arm, mid-thigh circumference; tricep, bicep and subscapular skinfolds) recorded at this visit.

## Randomisation

Eligible participants will be randomly assigned to active treatment with metformin or an identical looking placebo. This will be documented in the patient's paper case record and/or computer file to show the woman's participation in the trial.

Participants will be randomised via a web portal connected to a central randomisation facility based at the trial data centre, the Edinburgh Clinical Trials Unit, University of Edinburgh. Baseline eligibility data will be required before randomisation. Participants will be randomised in a 1:1 ratio to metformin or placebo. Randomisation will be stratified by treatment centre and BMI 30–39 vs >40 kg/m^2^.

## Concealment of allocation

Randomising participants to active or placebo tablets will achieve concealment of allocation. Placebo tablets will appear identical to active treatment, so that the participant is masked to treatment allocation. The outcomes will be measured by clinicians and investigators masked to treatment allocation. Masking will not be broken until after data entry is complete, the validity of the data is checked, all queries resolved, the patient populations agreed and the database locked. Any clinically indicated emergency unmasking will be recorded prospectively.

## Intervention

Metformin tablets (or matched placebo) 500 mg administered from as soon as practicable after the point of randomisation (and certainly between 12 and 16 weeks’ gestation) until delivery of the baby. The dose regimen is as follows: week 1, 500 mg once daily; week 2, 500 mg twice a day; week 3, 500 mg three times a day; week 4, 500 mg morning and lunchtime and 1000 mg in the evening; week 5 until delivery of the baby, 1000 mg in the morning and evening and 500 mg at lunchtime. All doses are taken with food and dose escalation should continue to either the maximum tolerable dose or 2500 mg, whichever is higher.

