## Objectives

### Primary objective

To determine the efficacy of metformin (up to 2500 mg daily), given to obese pregnant women from between 12 and 16 weeks’ gestation until delivery, in reducing gestational age-adjusted and sex-adjusted birthweight centile of the baby.

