### Dose changes

The local investigator or participant may alter the treatment regimen at his/her discretion, so long as the maximum daily dose does not exceed 2500 mg. Changes to the treatment dose will be recorded in the electronic case report form (eCRF) as soon as practicable.

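### The escalation rule ends at the higher of the tolerable dose and 2500 mg; it should end at the lower

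*Protocol article*

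**What the plan says.** The Intervention section sets out a five-step weekly escalation. The fourth step is "week 4, 500 mg morning and lunchtime and 1000 mg in the evening" and the last is "week 5 until delivery of the baby, 1000 mg in the morning and evening and 500 mg at lunchtime". The section then gives the rule for when escalation ends: "dose escalation should continue to either the maximum tolerable dose or 2500 mg, whichever is higher".

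Two other places bear on the same dose. The Dose changes section says that the "investigator or participant may alter the treatment regimen at his/her discretion, so long as the maximum daily dose does not exceed 2500 mg". The primary objective begins "To determine the efficacy of metformin (up to 2500 mg daily". Nothing in the article allows more than 2500 mg a day.

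**The concern.** A rule that names both a tolerability limit and a fixed maximum normally stops at whichever is reached first, which is the smaller of the two. The article says the larger. Taken at its word, that has two consequences:

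- Below 2500 mg, the tolerability limit never operates. Escalation continues to 2500 mg whatever the woman tolerates.
- Above 2500 mg, the fixed maximum never operates, although the article treats it elsewhere as a cap.

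This is the end-of-escalation instruction for a drug given to pregnant women without diabetes at seventeen hospitals. It should be right as written, and safe dosing should not depend on a reader noticing that it conflicts with the next section. Anyone who copies the regimen from the article would copy the error. What is at stake is the correctness of a dosing instruction, not the trial's inference.

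**Working it through.** **Inputs.** The weekly doses and the stopping rule come from the Intervention section, the cap from Dose changes, and the dose range from the primary objective. The article gives no distribution of maximum tolerable doses (MTD). The values below are therefore the schedule's own five steps, plus one illustrative value of 3000 mg.

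**Step 1: reproduce the 2500 mg figure.** Daily totals of the schedule:

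- Week 1: 500 mg
- Week 2: 2 × 500 = 1000 mg
- Week 3: 3 × 500 = 1500 mg
- Week 4: 500 + 500 + 1000 = 2000 mg
- Week 5 to delivery: 1000 + 500 + 1000 = 2500 mg

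The top step equals the stated 2500 mg, and no higher step is defined.

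**Step 2: compare the two wordings.** As written, end dose = max(MTD, 2500). With *lower*, end dose = min(MTD, 2500).

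| MTD (mg/day) | As written | With *lower* | Result of the literal rule |
|---|---|---|---|
| 500 | 2500 | 500 | 2000 above the tolerated dose |
| 1000 | 2500 | 1000 | 1500 above the tolerated dose |
| 1500 | 2500 | 1500 | 1000 above the tolerated dose |
| 2000 | 2500 | 2000 | 500 above the tolerated dose |
| 2500 | 2500 | 2500 | wordings agree |
| 3000 (illustrative) | 3000 | 2500 | 500 above the cap |

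**Step 3: set the results against the rest of the article.** The two halves of the table fail for different reasons.

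- MTD above 2500 mg: the literal rule contradicts the cap ("so long as the maximum daily dose does not exceed 2500 mg"), the range in the primary objective and the top of the schedule.
- MTD below 2500 mg: a ceiling of 2500 mg is not itself breached. The fault here is that escalating past the maximum tolerable dose contradicts the meaning of the term and leaves it with no function.

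The literal rule respects both limits only when the MTD is exactly 2500 mg. With *lower*, the end dose exceeds neither limit at any MTD, and it agrees with all three other statements.

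**The case against.** The strongest reply is that the rest of the article already neutralises the word. The schedule has no step above 2500 mg and Dose changes caps the daily dose there, so the upper failure cannot occur in practice. For the lower failure, "The local investigator or participant may alter the treatment regimen at his/her discretion", so nothing forces a woman past what she tolerates. On this view the overshoots in the table are arithmetic on a literal reading, not doses that anyone would receive. The slip is editorial, it has no bearing on the intention-to-treat comparison, and with 449 women already randomised by January 2014 the correction amounts to an erratum. The full protocol, which may have the right word, is not shown.

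Most of this stands as a limit on the consequences. The overshoots do describe the literal rule only, and no harm to any participant can be inferred from them. The reply does not rescue the sentence. The Dose changes section grants permission to depart from the regimen, whereas the Intervention section states what should be done. A cap combined with discretion is also not a rule that escalation stops at the tolerated dose. Nor can *higher* be read as a target of at least 2500 mg, since the cap forbids anything above it. Recruitment being advanced lowers the value of the correction for this trial but does not make the published rule correct.

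**Conclusion.** The stopping rule is wrong as written, and *lower* is the only word that fits the rest of the article. This rests on the article's own text and needs no outside figure. At the schedule's lower steps, the literal rule ends 500 to 2000 mg a day above the tolerated dose. Above 2500 mg, it breaks the stated cap, although the schedule never reaches that range.

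The number of women concerned cannot be stated, because the article does not say how many fail to tolerate 2500 mg. It does not show that anyone was dosed differently because of the wording. It also cannot show whether the slip is confined to the article. Sample size, power and the primary analysis are unaffected. The point is worth correcting because it is a dosing instruction in pregnancy, the error is plain and the remedy is nearly free.

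**What to change.** In the last sentence of the Intervention section, replace *higher* with *lower*, so that the end dose is min(maximum tolerable dose, 2500 mg). Then confirm that the full protocol and the dosing instructions held at the sites carry that wording, and correct them if they do not.

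The cost is one word and one document check. The schedule, data collection, sample size and analysis stay as they are.

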### Dose changes

The local investigator or participant may alter the treatment regimen at his/her discretion, so long as the maximum daily dose does not exceed 2500 mg. Changes to the treatment dose will be recorded in the electronic case report form (eCRF) as soon as practicable.

### Other medications

Alcohol is prohibited due to the increased risk of lactic acidosis. Iodinated contrast agents may increase the risk of renal failure; hence, if they are required, metformin should be discontinued for at least 48 h from immediately prior to contrast agent administration until after renal function has been re-evaluated and found to be normal. Clinicians prescribing glucocorticoids (systemic and local routes), β2-adrenoreceptor agonists and ACE inhibitors should be aware that they might amplify or diminish the hypoglycaemic effect of metformin.

## Study assessments

Following randomisation, study assessments for glucose tolerance testing and other tests will occur as detailed in table 3.

**Table 3 BMJOPEN2014006854TB3:** Summary of study visits

Visit number	1	2	3	4	5	6	7	8	9
Gestation	10–16 weeks	10–16 weeks	12–16 weeks	18–20 weeks	28 Weeks	36 Weeks	Term	Labour/delivery/neonatal	3 months postnatally
	Screening	Consent	Randomisation	Study visit (could be by telephone)	Study visit	Study visit	Study visit (could be by telephone)	Study visit	Study visit
Review inclusion and exclusion criteria	**X**								
Patient information leaflet	**X**								
Consent form		**X**							
Demographics		**X**							
Medical history		**X**							
Height and weight		**X**							**X**
Maternal anthropometry		**X**				**X**			**X**
Bloods for liver function/renal function/full lipid profile/CRP		**X**				**X**			
75 g OGTT (sampling at baseline and 2 hours)		**X**			**X**	**X**			
Stored sample for inflammatory and metabolic indices		**X**			**X**	**X**			
Randomisation			**X**						
Study drug dispensed			**X**		**X**				
Unused study drug/packaging returned								**X**	
Review SAEs				**X**	**X**	**X**	**X**	**X**	
Complete side effects questionnaire on eCRF				**X**	**X**	**X**	**X**	**X**	
Review and record pregnancy complications				**X**	**X**	**X**	**X**	**X**	
Saliva samples for cortisol measurements			X		X	X			
Bodpod measurements		X (OR VISIT 3)	X (OR VISIT 2)			X			X
Hyperinsulinaemic euglycaemic clamp						X			
FMD			X			X			
MR scan					X	X			
Labour/delivery information including birth weight, mode of delivery, EBL								X	
Cord blood and placenta biopsy								X	
Myometrium biopsy (if delivered by CS)								X	
Adipose tissue biopsy								X	
Baby's weight and anthropometry								X	X
Peapod measurements								X	X

CRP, C reactive protein; CS, caesarean section; EBL, estimated blood loss; eCRF, electronic case report form; FMD, flow mediated dilatation; OGTT, oral glucose tolerance test; SAE, serious adverse event.

Maternal anthropometric measurements recorded at baseline, 36 weeks’ gestation and 3 months postpartum, will include waist; hip; upper arm and thigh circumference and bicep, tricep and subscapular skinfold thickness. Neonatal anthropometric measurements recorded within 72 h of birth and at 3 months of age will include head circumference, and tricep and subscapular skinfold thickness. Length and weight will be recorded in order to calculate ponderal index.

Fasting maternal blood samples obtained at baseline, 28 and 36 weeks’ gestation will be stored for future analysis of inflammatory and metabolic indices, including (but not limited to) insulin, C reactive protein (CRP), interleukin (IL)-6, leptin, plasminogen activator inhibitor (PAI)1/PAI2 ratio, cortisol, lipids and non-esterified fatty acids. Cord blood obtained at the time of delivery will also be taken for measurement of glucose and stored for future measurement of the inflammatory and metabolic indices listed previously.

Table 3 also documents the timing of the nested substudies in which a subgroup of participants will participate. A summary of these is given below.

### Saliva samples

Diurnal cortisol levels will be measured in saliva samples collected at baseline, 28 and 36 weeks’ gestation. Saliva will be collected in salivettes at bedtime and on waking. Samples will be stored at −80°C. Cortisol will be measured by ELISA.

### Body composition

Maternal fat mass will be measured using air displacement plethysmography (BOD POD, http://www.lifemeasurement.com) at baseline, 36 weeks’ gestation and 3 months postpartum. Neonatal fat mass will be measured using the same technique (PEA POD, http://www.lifemeasurement.com) within 72 h of birth and at 3 months of age.

### Hyperinsulinaemic euglycaemic clamp

A subgroup of women will undergo a hyperinsulinaemic euglycaemic clamp study at 36 weeks’ gestation to characterise the relative effects of metformin on hepatic and peripheral insulin sensitivity.

### Flow-mediated dilatation

Endothelium-dependent flow-mediated dilatation will be measured in a subgroup of participants at baseline and again at 36 weeks’ gestation. Change in diameter of the brachial artery following a flow stimulus created by arterial occlusion will be measured using continuous two-dimensional grayscale ultrasound imaging.

### MRI and spectroscopy

A subgroup of participants will be scanned at 28 and 36 weeks’ gestation using a Verio 3 Tesla MRI system. T1-weighted acquisitions will be used to measure maternal subcutaneous and visceral fat; fetal liver volume; and fetal subcutaneous fat. Images will be analysed using the software program SliceOmatic. This program uses knowledge-based image processing to label pixels as fat or non-fat components and the adipose tissue mass derived using a mathematical model. Hepatic and skeletal muscle lipid content will be measured using ^1^H-magnetic resonance spectroscopy.

### Myometrial biopsies

A biopsy of the lower segment myometrium will be obtained from consenting participants who are delivered by caesarean section. The biopsies will be divided, with one portion placed in physiological saline for contractility studies and the other snap frozen for glycogen storage measurements.

## Participant compliance

Compliance will be recorded in a treatment diary and by counting of unused tablets. Additionally, gas chromatography mass spectrometry will be used to analyse metformin levels in blood samples from participants in the third trimester.

## Outcomes

### Primary outcome

Z-score corresponding to the gestational age-adjusted and sex-adjusted birthweight centiles of the baby.

### Secondary outcomes

Maternal insulin resistance at 36 weeks’ gestation, which will be correlated with adverse pregnancy outcomes.Maternal anthropometry and body composition at 16 and 36 weeks’ gestation and 3 months postpartum.Baby anthropometry and body composition at birth and 3 months of age.Maternal inflammatory markers, lipid and fatty acid indices prior to starting treatment and again at 28 and 36 weeks’ gestation including CRP, IL-6, leptin, lipid profile, non-esterified fatty acids, polyunsaturated fatty acids and PAI1/PAI2 ratio.Neonatal CRP, glucose, insulin and other inflammatory and metabolic indices as previously described (measured in cord blood at birth).Incidence of low birthweight centile.Gas chromatography mass spectrometry measurement of metformin in maternal plasma to determine adherence.Secondary outcomes from nested substudies;
Maternal salivary cortisol levels at baseline, 28 and 36 weeks’ gestation.Hepatic and peripheral insulin sensitivity at 36 weeks’ gestation as measured by the hyperinsulinaemic euglycaemic clamp technique.Maternal brachial artery endothelium flow-mediated dilatation measured at 16 and 36 weeks’ gestation.Maternal subcutaneous and visceral adipose tissue deposition and hepatic and skeletal muscle ectopic fat deposition assessed using MRI and magnetic resonance spectroscopy.Fetal liver volume and fetal subcutaneous fat deposition assessed using MRI.In vivo measurements of myometrial contractility on myometrial biopsies obtained at the time of caesarean section.Placental glucocorticoid receptor and 11 βHSD 1 (β hydroxysteroid dehydrogenase 1) and 2 mRNA levels.

## Side effects and adverse events reporting

Participants are instructed to contact their investigator at any time after consenting to randomisation if any symptoms develop. In the case of any events, the investigator will initiate the appropriate treatment according to their medical judgement. Participants with adverse events (AEs) present at their last visit will be followed up until resolution of the event. All AEs and serious AEs (SAEs) that occur after randomisation will be recorded in detail in the participant's medical notes. SAEs occurring in the mother or baby from the time a participant is randomised until 30 days after stopping taking study treatment or until 28 days after delivery (whichever is later) will be reported to the co-sponsors using the trial documentation. The standard definition of a SAE will be used.^35^ For the purposes of this study the following events will not be considered SAEs: miscarriage; preterm labour; preterm prelabour spontaneous rupture of membranes; preterm delivery in the maternal interest; preterm delivery in the fetal interest; hospitalisation for pregnancy-induced hypertension; hospitalisation for maternal discomfort; hospitalisation for rest; hospitalisation for observation or monitoring for which the woman is admitted for a period of less than 12 h; delivery complications such as caesarean section or postpartum haemorrhage; admission of the baby to the neonatal unit for a period of up to 14 days.

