### Secondary objectives

To determine the pattern of association between insulin resistance and adverse pregnancy outcomes, including incidence of pregnancy-induced hypertension, pre-eclampsia, caesarean section, postpartum haemorrhage, maternal weight gain during pregnancy and incidence of the baby's admission to the neonatal unit.To determine the effect of metformin on maternal body composition.To determine the effect of metformin on neonatal body composition.To determine the effect of metformin on maternal inflammatory and metabolic variables (measured at 28 and 36 weeks’ gestation) and on neonatal inflammatory variables (measured in cord blood at birth).To confirm that metformin does not increase the rate of babies with a low birthweight centile.To determine the efficacy (as opposed to the effectiveness) of metformin when analysis is restricted to those with pharmacological circulating levels of drug.A series of nested substudies will also be performed with the following objectives:
To determine the effect of metformin on maternal cortisol levels in obese pregnant women.To determine the effect of metformin in hepatic and peripheral insulin sensitivity at 36 weeks’ gestation in obese pregnant women.To determine the effect of metformin on endothelium-dependent flow-mediated dilatation in obese pregnant women.To determine the effect of metformin on maternal subcutaneous and visceral adipose tissue deposition and hepatic and skeletal muscle ectopic fat deposition during pregnancy.To determine the effect of metformin on fetal liver volume and subcutaneous fat deposition.To determine the effect of metformin on myometrial contractility and myometrial glycogen storage in obese pregnant women.To determine the effect of metformin on placental glucocorticoid receptor and 11 βHSD 1 and 2 mRNA levels.

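### The SAE exemption list makes no exception for life-threatening or suspected drug-related events, so it conflicts with the standard definition adopted just before it

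*Protocol article*

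**What the plan says.** All of the reporting rule is in one paragraph of the protocol article, under the heading on side effects and adverse events reporting.

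- **Definition.** "The standard definition of a SAE will be used". Its content is given by citation only.
- **Route.** SAEs in mother or baby are reported to the co-sponsors. The period runs from randomisation until 30 days after stopping treatment or 28 days after delivery, whichever is later. All AEs, serious or not, are recorded in the participant's medical notes.
- **Exemptions.** "For the purposes of this study the following events will not be considered SAEs: miscarriage; preterm labour; preterm prelabour spontaneous rupture of membranes". The list continues with preterm delivery for maternal or for fetal reasons, then "hospitalisation for pregnancy-induced hypertension; hospitalisation for maternal discomfort; hospitalisation for rest", then "hospitalisation for observation or monitoring for which the woman is admitted for a period of less than 12 h", and ends with "delivery complications such as caesarean section or postpartum haemorrhage; admission of the baby to the neonatal unit for a period of up to 14 days".

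Elsewhere, the table of study visits provides for review of pregnancy complications and a side-effects questionnaire at visits 4 to 8, and for mode of delivery and estimated blood loss at visit 8. The section on committee oversight names an independent Data Monitoring Committee.

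**The concern.** Exempting expected obstetric events from SAE reporting is reasonable in a pregnancy trial: routine caesarean sections and short neonatal stays would otherwise flood the system. Such a list normally removes events that are serious only because the woman or baby was in hospital. This one is worded differently. It says that the listed events are not SAEs, and it leaves no way back for a listed event that is serious for another reason or that the investigator suspects the study drug caused.

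The individual SAE report is at stake, since it is the only route to the co-sponsors that the article describes. Visit forms and the medical notes record that an event happened. The article does not say that they prompt a case-level report, or a judgement on relatedness, while the trial is running.

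**Working it through.** No figure in the plan needs reproducing and no arithmetic beyond a count applies. The check sets the definition beside the list and follows example events through both.

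**Step 1. Inputs.** The definition, the reporting route and the list all come from the side effects and adverse events section. The other routes of capture come from the visit table and the committee section. One assumption is needed: the cited standard definition has its usual content, so that death, a life-threatening event, hospitalisation or its prolongation, and disability each make an event serious.

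**Step 2. Classify the 11 items.**

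| Item | Worded as | Limit stated |
|---|---|---|
| Miscarriage | event | none |
| Preterm labour | event | none |
| Preterm prelabour membrane rupture | event | none |
| Preterm delivery, maternal reasons | event | none |
| Preterm delivery, fetal reasons | event | none |
| Delivery complications, including postpartum haemorrhage | event | none |
| Admission for pregnancy-induced hypertension | admission | none |
| Admission for discomfort | admission | none |
| Admission for rest | admission | none |
| Admission for observation or monitoring | admission | under 12 h |
| Neonatal unit admission | admission | up to 14 days |

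Six items exempt the event itself and five exempt an admission (6 + 5 = 11). Nine have no limit and two are limited by duration (9 + 2 = 11). None has an exception for seriousness beyond hospitalisation, and none has one for suspected relation to study drug. The delivery item is also open-ended, because haemorrhage and caesarean section are given only as examples: "delivery complications such as caesarean section or postpartum haemorrhage".

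**Step 3. Follow example events through the rule as printed.**

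- *Life-threatening postpartum haemorrhage.* It meets the assumed definition. It is also a listed delivery complication, so it is declared not to be an SAE and is not reported as one. The two sentences give opposite answers.
- *Admission for discomfort that the investigator suspects is drug-related.* It meets the definition through hospitalisation. It is listed, and suspicion of a drug cause does not change that, so it is not reported as an SAE.
- *Neonatal unit stay of up to 14 days suspected to be drug-related.* The admission is exempt in the same way.
- *Drug-related hospitalisation for a reason not on the list.* Still an SAE and still reported.
- *Neonatal unit stay beyond 14 days, or a neonatal death.* Still an SAE and still reported. The list exempts a shorter admission and names no neonatal death.

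**Step 4. Other capture.** Haemorrhage is visible through estimated blood loss at visit 8. Hypertensive disorders can be picked up in the review of pregnancy complications, and symptoms in the side-effects questionnaire. These supply data on the events. The article does not describe any of them as a substitute for an individual report to the co-sponsors.

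**The case against.** The strongest reply is that this is a journal article. It defines an SAE by citation and refers to trial documentation, and the full protocol may well provide for related or life-threatening events. That possibility is real and affects the fix. It does not remove the point, because the article prints the exemption as an unqualified rule. The objection is to what is stated, and not to a detail left out.

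Second, the five admission items can fairly be read as exempting only the hospitalisation, so that the illness behind it stays reportable if serious on other grounds. This stands in part. It answers the worry about a gravely ill baby, but not the case of an admission that is serious only as a hospitalisation and is suspected to be drug-related. Nor does it help with the six items that exempt the event itself.

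Some stronger readings are tempting, and the document does not support them:

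- *That exempt events never reach the co-sponsors.* The text removes them from SAE reporting only. They are in the notes and partly on trial forms, and a Data Monitoring Committee oversees safety.
- *That drug-related admissions in general go unreported.* Only admissions in the listed categories are affected.
- *That the admission items contradict one another, because observation has a 12-hour limit and discomfort and rest have none.* These are different reasons for admission. A single duration rule would be a preference.
- *That haemorrhage deserves special concern because a substudy examines myometrial contractility.* The protocol presents this as a mechanistic objective ("To determine the effect of metformin on myometrial contractility and myometrial glycogen storage in obese pregnant women") and nowhere says that metformin is expected to affect bleeding.

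**Conclusion.** The point holds in a limited form. As printed, the definition and the exemption list disagree about any listed event that is serious beyond hospitalisation, and the list also removes listed events suspected to be related to study drug. Such events would not be reported to the co-sponsors as SAEs.

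The size can be stated only as a count of rules: 0 of the 11 items have either exception. The article gives no rates for haemorrhage, neonatal admission or the other events, so the number of missed reports cannot be estimated. Comparing the 14-day neonatal limit with the length of the reporting period would not help, since that ratio says nothing about how many events go unreported.

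The conclusion rests on two assumptions: that the cited definition has its usual criteria, and that the wording printed here is the rule investigators follow. If the full protocol already contains the exceptions, the problem shrinks to a mismatch of wording. The point concerns safety reporting and leaves the primary comparison untouched. The change is worth making because it is small and protects individual case review.

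**What to change.** Reconcile the two sentences and keep the list:

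1. State that the listed events are exempt only when they are serious solely because of hospitalisation or its prolongation.
2. State that a listed event that meets any other seriousness criterion, or that the masked investigator suspects is related to study drug, is still reported as an SAE.
3. If the full protocol already provides for this, confirm it and bring the article's wording into line.

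This takes about a sentence in the protocol and matching guidance for completing the SAE form. The downside is a modest number of additional SAE reports. Uncomplicated caesarean sections, short neonatal stays and brief admissions that raise no other concern stay exempt.
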